### Primary outcome measure

The primary outcome measure is daily physical activity (daily step count and percentage of day spent in sedentary activities). Participants will wear an activity monitor (activePAL™) for seven consecutive days. Data from the device will be recorded and uploaded to a computer. These data will be averaged over the 7 days of activity to calculate a daily step count. The percentage of the day spent in sedentary activities will also be recorded. This measure will be taken upon entry to the study (test 1), and at approximately 6 months (test 2), and then at 6 months after surgery (test 3).

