Physical activity interventions based on social psychological theory are more effective than atheoretical ones in promoting health-protective behaviour [13]. In addition, interventions are more cost-effective when they have theoretically devised approaches and clearly measurable constructs. A theoretical basis for the intervention components and inclusion of key psychological measures based on theory can demonstrate *how* the intervention works, highlighting the processes by which behaviour change occurs [14]. The Health Action Process Approach (HAPA) [15] stipulates a dual-phase approach to action: a *motivational* phase (i.e. outcome expectancy, risk perception, action self-efficacy and intention) and a *volitional* phase (i.e. maintenance self-efficacy, recovery self-efficacy, action planning, coping planning and action control). According to HAPA, intention is a necessary but insufficient condition for action initiation and persistence. People also need to identify effective volitional self-regulatory strategies to enact their intentions and prevent relapse. The effectiveness of HAPA-based interventions has been demonstrated in multiple populations and contexts and across multiple health behaviours [15–21]. The use of this framework to promote physical activity in people with OA does not appear in the literature. However, HAPA has recently been used to identify six physical activity attributes that are most salient to adults with knee OA [22], which supports this framework in this population.

This report describes the methodology of the ENHANCE trial, a randomised controlled trial to test the effectiveness of the ENHANCE programme for a usual care control group. This study seeks to test the hypothesis that the combination of a targeted exercise prescription with behaviour change counselling based on HAPA will be more effective than usual care in increasing the number of daily steps at all-time points after intervention. Concurrently less pain, improved function and reduced metabolic and cardiovascular risks factors will be recorded.

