### Sample size

The sample size has been determined to be 50 patients in each group to detect an increase of 1200 (24%) daily steps (alpha 0.05, power 0.8) based on research indicating usual changes in step count after lower limb joint replacement [10]. The study that our sample size calculations are based upon experienced a low withdrawal rate of 4%. We have made a conservative estimate of a 10% withdrawal rate and, hence, will recruit 110 participants.

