### Data analysis

Differences in primary and secondary outcomes between groups will be compared using an intention-to-treat analysis. Once a participant is randomised to a study group, they will be considered a trial participant and analysed according to their allocated group, regardless of missing data for follow-ups or the amount of intervention received. Bivariate relationships will be tested with Pearson or Spearman correlations, independent *t*-tests or Mann–Whitney *U* tests (to examine relationships between the dependent variables and the independent variables) or chi squared tests for categorical variables. Each primary and secondary outcome will be analysed using a two-way repeated-measures analysis of covariance (ANCOVA) to determine differences between groups (exercise versus usual care) and between time points (test 1, test 2 and test 3). In addition, effects of the intervention targeting the psychological HAPA-based constructs on regular exercise is tested along with the key processes (mediation) involved. Data will be analysed with a linear mixed model with condition as between-participants effects and time points as within-participants effects. A path analysis will be used to determine mediation effects. Data analysis will be performed using statistical software STATA (STATA 13, Stata Corp, College Station, TX, USA) and Mplus. Statistical significance is set at *p* < 0.05 for all analyses.

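### Two primary variables, an unadjusted 0.05 throughout and no named deciding comparison: if either variable may carry the claim, the primary false-positive rate exceeds 5%

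*Protocol article*

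**What the plan says.** - **Primary outcome measure:** "The primary outcome measure is daily physical activity (daily step count and percentage of day spent in sedentary activities"). After baseline, both variables are recorded "at approximately 6 months (test 2), and then at 6 months after surgery (test 3"). The Abstract gives the same pair. Neither variable and neither time is put first.
- **Data analysis, model:** "Each primary and secondary outcome will be analysed using a two-way repeated-measures analysis of covariance (ANCOVA) to determine differences between groups" and "between time points (test 1, test 2 and test 3"). This is one model per outcome. The section does not say whether the group effect, the group-by-time interaction or a contrast at one time decides.
- **Data analysis, level:** "Statistical significance is set at *p* < 0.05 for all analyses". No adjustment, testing order or both-must-succeed rule accompanies it.
- **Background, hypothesis:** the programme will be "more effective than usual care in increasing the number of daily steps at all-time points after intervention". Sedentary time is not part of the hypothesis.
- **Sample size:** "50 patients in each group to detect an increase of 1200 (24%) daily steps (alpha 0.05, power 0.8"). Only steps are sized, and no time point is given.

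**The concern.** Sedentary percentage is primary in the Abstract and in the outcome section, but absent from the hypothesis and the sample size. With 0.05 applied to everything, the text would allow a positive primary claim on sedentary percentage alone, for which no power was planned. It would also allow one on steps at whichever follow-up happens to succeed.

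The two follow-ups answer different questions: one falls about six months after baseline, the other six months after joint replacement. Choosing between them after seeing the data would therefore matter. The alpha and power in the sample size section belong to a single comparison of steps, and the article does not say which comparison that is.

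**Working it through.** **1. The plan's own figure.** The inputs are 50 per group, a difference of 1200 steps, alpha 0.05 (two-sided assumed) and power 0.80. No SD is printed, so 50 cannot be reproduced forwards. Solving n = 2·SD²·(1.960 + 0.842)² / 1200² for n = 50 gives SD = 1200 / (2.802 × √(2/50)) ≈ 2142 steps (about 2121 with a t-test). The figure describes one two-group comparison of steps, made once.

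**2. One deciding test per outcome, either sufficient (two tests).** If independent, the error is 1 − 0.95² = 9.75%. For correlated test statistics I simulated two-sided tests on bivariate normal statistics under no effect. The correlations are assumptions.

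| Correlation between outcomes | Chance of at least one p < 0.05 |
|---|---|
| 0 | 9.75% |
| 0.5 | 9.1% |
| 0.7 | 8.4% |
| 0.9 | 7.0% |

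**3. Each outcome also read at each follow-up, any one sufficient (four tests).** If independent, the error is 1 − 0.95⁴ = 18.5%. Correlated cases were simulated in the same way.

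| Correlation between outcomes / between times | Chance of at least one p < 0.05 |
|---|---|
| 0 / 0 | 18.5% |
| 0.5 / 0.5 | 16.1% |
| 0.5 / 0.6 | 15.6% |
| 0.7 / 0.7 | 13.7% |
| 0.9 / 0.9 | 9.8% |

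**4. Steps must succeed at both follow-ups.** Each test is held at 5%, so their joint success cannot exceed 5% under any null. Power is the open question.
- If each test has exactly 0.80 power (mean z of 2.802), joint power is 0.80² = 0.64 at test correlation 0, 0.70 at 0.6 and 0.75 at 0.9.
- Suppose instead that 2142 is a raw SD, baseline is the covariate, and all pairwise correlations between visits are 0.5. The mean z becomes 2.802 / √(1 − 0.5²) = 3.235, and power per time is Φ(3.235 − 1.960) ≈ 0.90. The correlation between the two tests is (0.5 − 0.25) / (1 − 0.25) = 0.33, and joint power is about 0.82.
- With all correlations at 0.6, joint power is about 0.89.

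**5. Price of keeping several primaries with Bonferroni, unadjusted comparison, SD 2142.**
- Two tests at 0.05/2 = 0.025: power at 50 per group is about 71%, and 80% power needs about 61 per group.
- Four tests at 0.05/4 = 0.0125: power is about 62%, and 80% power needs about 72 per group.

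**The case against.** The strongest reply is that the article already singles out steps. The hypothesis concerns steps at every post-intervention time, and the sample size uses steps only. On that reading steps lead, both follow-ups must succeed, and no error is inflated. A separate analysis plan might also fix the contrast and the testing order.

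Part of this stands. The deciding contrast is a detail an analysis plan could supply, and the hypothesis can be read as requiring both times. But the article itself labels two variables primary and fixes 0.05 for all analyses. An analysis plan that named one primary, or split alpha, would have to change that text.

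Two stronger readings are tempting, and the article supports neither.
- **A threefold false-positive rate.** A reader might infer four separate tests and an error near 15%. The Data analysis section prescribes one repeated-measures model per outcome, not a test at each follow-up. With one deciding effect per outcome, the inflation is at most about twofold (9.75%). Three times 5% needs four tests to count, any one to suffice, and moderate correlations. Both variables come from the same monitor over the same seven days, so high correlation is plausible.
- **A definite loss of power.** A reader might infer that requiring both follow-ups takes power below 80%. The figure of 0.70 assumes exactly 0.80 at each time and a test correlation of 0.6. The article gives no SD and does not say whether it refers to raw or change values, and the planned ANCOVA may gain precision from baseline. Step 4 shows that joint power could lie on either side of 0.80.

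**Conclusion.** The concern holds. The text fixes two primary variables and an unadjusted 0.05 without saying which result decides, while hypothesis and sample size cover steps alone.

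- If either variable may carry the claim, the error exceeds 5% at every correlation examined: about 7% to 9.8% with one deciding test per outcome, and about 10% to 18.5% if the follow-ups are also read separately with any one sufficient.
- If steps must succeed at both follow-ups, error is controlled, but 80% power is not demonstrated for that claim.

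The ranges rest on assumed correlations of 0.9 to 0, two-sided tests and normal test statistics. The conclusion that error exceeds 5% when either variable suffices does not depend on a particular correlation in that range.

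**What to change.** 1. In the Abstract and in Primary outcome measure, name daily step count as the single primary outcome, matching the hypothesis and the sample size.
2. In Data analysis, name one deciding comparison at 0.05 from the repeated-measures model. One option is the baseline-adjusted group difference in steps at test 2, with test 3 next in a fixed order that stops at the first non-significant result. Putting test 2 first is a choice, so the hypothesis in the Background, which covers every post-intervention time, must be reworded to match whatever is chosen. If success at both times is wanted, say so and size the trial for it.
3. Test sedentary percentage later in the fixed order, or report it as secondary with 95% confidence intervals.

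**Cost.** Sedentary percentage loses its co-primary label. The trial is registered and ongoing, so the registry entry needs a dated update before data are analysed. With a single lead comparison, steps keep the full 0.05 and no patients are added. Keeping several primaries under Bonferroni would carry the costs in step 5.

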### Secondary outcomes

The secondary outcomes include assessment of pain, function, general quality of life, clinical markers and psychological HAPA-based constructs. Specifically, tools to gather these data include measures of pain (visual analogue scale), quality of life (Short Form 12-item health survey on medical outcomes or SF-12), function (Oxford Hip and Knee Score) and Timed Up and Go. Clinical markers of comorbidities, such as cardiovascular and metabolic disease, will be assessed at all time points. Clinical markers relating to cardiovascular health (blood pressure), metabolic health (blood glucose and HbA1c) and body composition (waist circumference, body mass index and body fat percentage) will also be recorded. Psychological HAPA-based constructs (see potential mediators in Table 3) will be measured on multi-item psychometric instruments developed using standardised guidelines and validated in previous studies [15–21] and adapted for use in the current study. All secondary measures will be taken upon entry to the study (test 1), and at approximately 6 months (test 2), and then 6 months after surgery (test 3).

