Providing information on the risk factors of a sedentary lifestyle	Information provision Mental imagery	Risk perception
Providing information on the benefits and advantages of regular walking	Information provision Mental imagery	Positive outcome expectancy
Establishing confidence to start regular walking	Identification of resources Modelling (modelling by others) Mental imagery Verbal persuasion	Action self-efficacy
Formulating the intentions of regular walking	Intention formation Goal setting	Intention
Volitional component		
Making plans on when, where, how and with whom to conduct regular walking	Planning exercise	Action planning
Developing strategies to cope with the barriers that may interfere with regular walking	Identification of barriers Problem-solving	Coping planning
Developing confidence in maintaining regular walking with barriers, as well as resuming regular walking if interrupted	Mental imagery Mastery experience (past experience)	Maintenance self- efficacy Recovery self-efficacy
Developing strategies to remind and monitor regular walking	Self-monitoring exercise Reminders and sign-in table	Action control

*HAPA* Health Action Process Approach

Participants work with the AEP to identify small, gradual changes to exercise patterns that can be mastered and maintained, rather than drastic changes that are less likely to be maintained over time. This facilitates a sense of mastery and confidence, which can be built upon throughout the intervention to build self-efficacy. Each intervention contact results in a behaviourally specific action plan that specifies exactly what the participant intends to do and when. Also in the contact sessions, barriers and supports are identified, confidence is assessed and problem-solving is discussed as necessary. These steps are repeated during intervention counselling sessions, with goals being adjusted as necessary. Participants are encouraged to set their own goals based on their fitness level and circumstances.

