
### Assessment of psychological HAPA-based constructs

*Regular exercise* will be assessed using a multi-item scale. ‘Think about the past week. In general, how often did you do regular exercise?’ Responses are rated from 1 (never) to 4 (very often). ‘Think about the past week. In general, to what extent did you do regular exercise?’ Responses are rated from 1 (never) to 4 (a large extent). In addition, an open format item ‘Think about the entire past week and count, how many days you did exercise (e.g., if you exercised for at least 20 minutes at a time every day then the response is 7)?’*Habit strength* is assessed using the four-item Self-Report Behavioural Automaticity Index [38]. A sample item is ‘Do you agree that doing regular exercise is something… I do automatically?’ Responses are rated from 1 (strongly disagree) to 7 (strongly agree).*Intention* is assessed with three items. A sample item is ‘In regards to doing regular exercise over the next week, do you agree that… I intend to exercise?’ Responses are rated from 1 (strongly disagree) to 7 (strongly agree).*Attitude* is assessed with three items. A sample item is ‘Doing regular exercise over the next week would be… unpleasant.’ Responses are rated on semantic differential scales from unpleasant to pleasant, bad to good, or harmful to beneficial.*Social influence* is assessed with four items. A sample item is ‘In regards to doing regular exercise over the next week, do you agree that… People give me support to ensure I regular exercise?’ Responses are rated from 1 (strongly disagree) to 7 (strongly agree).*Perceived Behavioural Control* is assessed with four items. A sample item is ‘In regards to doing regular exercise over the next week, do you agree that… I have complete control over whether I do regular exercise?’ Responses were rated from 1 (strongly disagree) to 7 (strongly agree).*Barrier self-efficacy* is assessed with five items. A sample item is ‘I am confident I can do regular exercise over the next week… even when I am in pain.’ Responses are rated from 1 (not at all confident) to 7 (definitely confident).*Action planning* is assessed with four items. A sample item is ‘In regards to doing regular exercise over the next week, do you agree that I have made a plan regarding… When to regularly exercise?’ Responses are rated from 1 (not at all true) to 7 (definitely true).*Action control* is assessed with three items. A sample item is ‘During the last week… I have often had my regular exercise intentions on my mind?’ Responses are rated from 1 (not at all true) to 7 (definitely true).

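### Only three of the nine Table 3 mediators have a scale of the same name, three have none on any mapping, and mediation is tested on self-reported exercise rather than daily steps

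*Protocol article*

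**What the plan says.** The Secondary outcomes section of the protocol article defines the psychological constructs by pointing to Table 3: "Psychological HAPA-based constructs (see potential mediators in Table 3) will be measured on multi-item psychometric instruments". Table 3, in the section on the counselling programme, lists four motivational mediators (risk perception, positive outcome expectancy, action self-efficacy, intention) and five volitional ones (action planning, coping planning, action control, and the pair "Maintenance self- efficacy Recovery self-efficacy"). The Background describes HAPA with the same set; its volitional phase is "maintenance self-efficacy, recovery self-efficacy, action planning, coping planning and action control".

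The section on assessing HAPA-based constructs then goes through nine scales: regular exercise, habit strength, intention, attitude, social influence, perceived behavioural control, barrier self-efficacy, action planning and action control. Regular exercise is participants' own recall of the past week.

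The Data analysis section says that "effects of the intervention targeting the psychological HAPA-based constructs on regular exercise is tested along with the key processes (mediation) involved", using a path analysis. It does not name the step count as a mediation outcome and gives no lag between mediator and outcome.

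**The concern.** The Background gives the reason for measuring theory-based constructs: to show how the programme works. That needs a measure of each construct the programme is meant to move, and an outcome that represents the behaviour of interest.

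Both parts look weak. The list of scales is not the list in Table 3, and some constructs without a scale are ones the programme deliberately targets. Table 2 schedules coping in sessions 3 and 5 and strategies for barriers in session 4. The counselling text includes relapse prevention, and Table 3 includes information on the risks of a sedentary lifestyle.

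The mediation outcome is also not the one in the hypothesis. The hypothesis concerns daily steps and Table 3 is written around walking, but the mediation analysis uses a questionnaire scale. The trial could report support for a HAPA mechanism that was only partly measured, on an outcome that shares its source with the mediators.

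**Working it through.** The plan gives no figure to reproduce. The check is a match of two lists, Table 3 against the assessment section.

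| Table 3 mediator | Scale of the same name | Nearest other listed scale |
|---|---|---|
| Risk perception | no | none |
| Positive outcome expectancy | no | attitude |
| Action self-efficacy | no | perceived behavioural control |
| Intention | yes, 3 items | – |
| Action planning | yes, 4 items | – |
| Coping planning | no | none |
| Maintenance self-efficacy | no | barrier self-efficacy, 5 items |
| Recovery self-efficacy | no | none |
| Action control | yes, 3 items | – |

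**Count, adding one equivalence at a time:**
- Names only: 3 measured, 9 − 3 = 6 not.
- Barrier self-efficacy taken as maintenance self-efficacy: 4 measured, 5 not.
- Attitude also taken as outcome expectancy: 5 measured, 4 not.
- Perceived behavioural control also taken as action self-efficacy: 6 measured, 3 not (3/9, one third).

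**How good are the equivalences?** The article states none of them. The first is close: the barrier item begins "I am confident I can do regular exercise over the next week" and goes on to pain as the obstacle, which fits the maintenance half of the Table 3 row on maintenance and recovery. The second is arguable, because the attitude scale includes a harmful-to-beneficial rating. The third is the loosest. Table 3 describes the action self-efficacy component as "Establishing confidence to start regular walking", while the sample item for perceived behavioural control asks about having control over exercising.

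**The other direction.** Five of the nine listed scales carry names that are not in Table 3: habit strength, attitude, social influence, perceived behavioural control and barrier self-efficacy. A sixth, regular exercise, is the behaviour itself. With the three matches this accounts for all nine (5 + 1 + 3 = 9).

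**The mediation outcome.** Four statements, set side by side:
- Data analysis: the mediation outcome is regular exercise.
- Assessment of HAPA constructs: regular exercise is self-reported.
- Randomisation: participants cannot be blinded.
- Primary outcome measure: the activity monitor is worn for seven days at each of the same three tests.

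Mediators and outcome therefore come from one questionnaire, answered by people who know their allocation. A tendency in the intervention arm to report favourably would raise the mediator scores and the exercise score together, and a path model would read that as an indirect effect. The monitor count does not share this source.

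One further feature matters if mediator and outcome are taken from the same visit. The exercise scale looks back over the past week, while the intention, attitude and barrier self-efficacy items look ahead to the next. Those mediators would refer to a period after the outcome.

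**The case against.** **The article may only be abbreviating.** The full questionnaire is not shown, and most scales are represented by an item count and one sample item. Unseen items could touch on coping or recovery. This has some weight, but the section goes construct by construct and gives space to constructs outside Table 3, so it reads as a different set and not a shortened one. The action planning sample item, "do you agree that I have made a plan regarding… When to regularly exercise", concerns when to exercise, which is action planning content. A few recovery items inside a five-item barrier scale would not, under one score, separate recovery from maintenance self-efficacy.

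**Table 3 is provisional.** It is headed as proposed components and potential mediators, and the instruments are said to be adapted. That is so, but the Secondary outcomes section still states that these mediators will be measured.

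**Most mediators have no scale.** A reader might infer this. It holds by name (6 of 9) and with the single closest equivalence (5 of 9), but not once attitude is also accepted (4 of 9). It should not be stated without the mapping.

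**The path analysis cannot show how the programme works, or has no time order.** A reader might infer this too. The documents do not support it. At least three mediators are measured at three tests, so a lagged model is possible. The Data analysis section does not commit to a same-visit model, and the choice of lag may properly sit in an analysis plan that is not shown.

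**Self-reported exercise is a legitimate outcome.** It matches the behaviour the scales ask about, an interviewer administers the questionnaires, and outcome assessors are blinded. All of this stands, and it is a reason to keep the scale. It does not remove reporting bias from unblinded participants or make the result an explanation of daily steps.

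**Conclusion.** The concern holds in limited form. The Secondary outcomes section and Table 3 promise nine mediators. The listed scales deliver three by name, four with one close equivalence, and six at most. The three without a counterpart on any mapping are enough to conclude that the whole Table 3 mechanism is not testable as described. For the constructs that are measured, mediation of self-reported exercise alone is weak evidence, because shared reporting bias is a competing explanation and the hypothesis is about steps. How large that bias would be cannot be derived from the article.

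The conclusion assumes that the assessment section lists the constructs in full and that regular exercise in the Data analysis section means the self-report scale of that name. It concerns a secondary, explanatory aim. The randomised comparison of steps and sedentary time is not touched.

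**What to change.** 1. **Reconcile the lists.** Limit the HAPA mediation claim to intention, action planning, action control and barrier self-efficacy, state which Table 3 construct the last represents, and declare the other Table 3 mediators untested. Adding short item sets for the missing constructs is an alternative only if baseline collection allows it. The trial is ongoing, and participants already enrolled would have no baseline value.
2. **Label the rest.** Report habit strength, attitude, social influence and perceived behavioural control as additional constructs outside Table 3. They need not be dropped: the counselling sessions address habits and social support.
3. **Add a mediation outcome.** Use the monitor-measured daily step count, adjusted for baseline steps and the baseline mediator, alongside self-reported exercise.
4. **Treat a lagged path as supplementary.** A path from the mediator at test 2 to steps at test 3 gives time order, but surgery falls between the tests and only participants who have had surgery and reached test 3 contribute. It should not be the only path.

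The cost is a narrower mechanism claim, somewhat more analysis and, if items are added, a slightly longer interview. The step data are already being collected.
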